### Secondary endpoints

2.9

The secondary endpoints are as follows:

(1)Technical success rateTechnical success is defined as the stent being positioned between the stomach and intrahepatic bile duct, as seen on CT performed 1 day after treatment.(2)Procedure-related adverse event (AE) rateProcedure-related AEs are defined as AEs judged to be “related,” “possibly related,” or “might be related” to the procedure. Procedure-related AEs will be divided into early AEs occurring within 14 days after treatment and late AEs occurring from 15 to 60 days after treatment. Early AEs may include postprocedural pancreatitis, cholangitis, stent migration, stent deviation, gastric ulcer associated with mechanical irritation of the stent, bleeding, gastrointestinal injury, and procedure-related deaths. Late AEs may include stent migration, stent deviation, stent occlusion, and gastric ulcer associated with mechanical irritation from the stent.(3)Procedure timeProcedure time is defined as the time from the puncture of the bile duct to stent placement.(4)Procedure success rate using only the HG01 systemProcedure success using only the HG01 system is defined as successful insertion of the stent into the left intrahepatic bile duct using only the HG01 system.(5)Stent patency rate at 30 and 60 days after treatmentThe stent patency rates are defined as the percentage of patients who do not experience stent dysfunction from the date of stent insertion to 30 and 60 days after treatment.Stent dysfunction is defined as follows.(1)A T-Bil level of ≥3.0 mg/dL when the lowest T-Bil level measured after treatment is <1.5 mg/dL.(2)A T-Bil level more than 2.0 times the lowest level when the lowest T-Bil level measured after treatment is more than 1.5 mg/dL.(6)Re-intervention success rate and re-intervention methodRe-intervention success is defined as the placement of a new drainage tube and improvement in the T-Bil level to below 50% of the highest pretreatment level within 21 days after re-intervention.The following re-intervention methods can be selected.(1)Treatment from the stent(2)Other EUS-guided biliary drainage(3)Trans-papillary biliary drainage(4)Percutaneous transhepatic biliary drainage(5)Surgical cholangiojejunostomy(7)Survival rate at 60 days after treatment(8)Distance of movement of the stent position at 1, 14, 30, and 60 days after treatmentThe length of the stent inside the stomach on the abdominal CT at day 0 after treatment will be compared with the length of the stent inside the stomach on days 1, 14, 30, and 60 after treatment, to evaluate the distance of movement of the stent from its placement position.

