### Data collection

2.11

Baseline assessment will be performed during the screening period. Basic information including sex, age, date of birth, primary disease and date of first diagnosis, history, concomitant disease, and metal allergy to nickel-titanium will be recorded. To ensure feasibility and safety, complete blood counts, hepatic and renal function tests, and biochemical tests will be performed during the screening period.

CT will be performed during the screening period to determine the site of biliary obstruction and the tumor stage according to the TNM classification.^[15]^ Patients will undergo the above-mentioned blood tests on postprocedural days 1, 3, 7, 14, 21, 30, and 60 to evaluate the efficacy of the treatment, AEs, and stent dysfunction. CT will be performed postoperatively on days 0, 1, 14, 30, and 60 to evaluate the position of the stent, AEs, and stent dysfunction. Esophagogastroduodenoscopy will be performed postoperatively on days 14 and 60 to evaluate gastric mucosal damage by the stent. All patients will be followed until either death or 60 days after the treatment to record survival, concomitant medications, and concomitant therapy. The schedule for enrollment, interventions, and assessments is shown in Figure 2.

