#### Statistical analysis

2.12.2

In the effectiveness analysis for the population, the full analysis set (FAS) is the main analysis, and the per protocol analysis set (PPS) acts as a reference. In the safety analysis for the target population, all test examples will be analyzed. For the clinical success rate, a test of the mother ratio against the threshold clinical success rate of 0.73 will be performed for the FAS. The exact method will be used to calculate the *P*-value, and a one-sided test will be performed. If the *P*-value is below the significance level of α = 0.05, EUS-HGS using the HG01 system will be considered effective. For the rates of technical success, procedure-related AE, successful procedures using only the HG01 system, and stent patency at 30 days, the percentages and 95% Clopper–Pearson confidence intervals will be calculated. For the procedure time, the mean and 95% confidence interval will be calculated. For the overall survival time, the survival rate will be estimated using the Kaplan–Meier method, and the 95% confidence interval at each time point will be calculated using Greenwood's formula. In addition, a Kaplan–Meier plot will be used to draw the survival curve. For the distance of movement of the stent position at 1, 14, 30, and 60 days after treatment, the mean and 95% confidence interval will be calculated. We will also create transition charts for each case and for the mean values. Error bars representing standard error will be added to the mean trend chart. The number and percentage of AEs will be calculated for each grade of AEs. All analyses will be performed using R version 4.1.2 (The R Foundation for Statistical Computing, Vienna, Austria).

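### Stent dysfunction is defined only by a bilirubin rise from the post-treatment nadir, so some non-working stents count as patent, and only one of the two patency time points has a stated analysis

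*Protocol article*

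**What the plan says.** Protocol article, Secondary endpoints (2.9), item 5, defines the patency rates as "the percentage of patients who do not experience stent dysfunction from the date of stent insertion to 30 and 60 days after treatment". Dysfunction then has two criteria and no others:

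- Rule 1: "A T-Bil level of ≥3.0 mg/dL when the lowest T-Bil level measured after treatment is <1.5 mg/dL".
- Rule 2: "A T-Bil level more than 2.0 times the lowest level when the lowest T-Bil level measured after treatment is more than 1.5 mg/dL".

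Item 2 of the same section treats mechanical failures as adverse events: "Late AEs may include stent migration, stent deviation, stent occlusion, and gastric ulcer associated with mechanical irritation from the stent". Re-intervention is item 6 and stent movement on CT is item 8. None of these enters the dysfunction definition.

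Data collection (2.11) states: "CT will be performed postoperatively on days 0, 1, 14, 30, and 60 to evaluate the position of the stent, AEs, and stent dysfunction".

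Statistical analysis (2.12.2) gives the estimator: "stent patency at 30 days, the percentages and 95% Clopper–Pearson confidence intervals will be calculated". It names no analysis of patency at day 60.

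**The concern.** A patency rate should separate working stents from failed ones. Here the only evidence of failure is a rise in T-Bil from the patient's own lowest post-treatment value. That has four consequences.

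- (a) A stent that never drains leaves a high nadir, and the high nadir sets a high bar for dysfunction.
- (b) A nadir of exactly 1.5 mg/dL falls under neither rule.
- (c) An occlusion or migration seen on CT or endoscopy, or one that leads to re-intervention, does not count unless T-Bil also crosses the threshold. Prompt re-intervention can keep T-Bil below it, so a failed stent stays patent. This sits badly with the stated purpose of the CT scans.
- (d) The endpoint has two time points and the analysis has one.

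The published patency rate could then include stents that did not work. The protocol's conclusion says the system is likely to become the first choice if efficacy and safety are confirmed, so readers will look at this figure.

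**Working it through.** The protocol states no planned patency figure, so there is none to reproduce. The check applies the two rules literally to illustrative T-Bil courses (mg/dL, invented for the test) at the scheduled blood-test days 1, 3, 7, 14, 21, 30 and 60 (section 2.11).

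**Threshold.** Let m be the post-treatment nadir. Dysfunction requires a later T-Bil of at least 3.0 if m < 1.5, or above 2.0 × m if m > 1.5. No threshold exists if m = 1.5.

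**(a) Never drained.** Inclusion criterion 5 requires T-Bil above 3.0, so a patient who does not drain falls under rule 2.
- Flat at 10: m = 10, threshold 20, ratio 10/10 = 1.0. Patent.
- Nadir 10, later 18: threshold 20, ratio 1.8. Patent.
- 9.8, 9.6, 10.2, 11.5, 13, 15, 18: m = 9.6, threshold 19.2, ratio 18/9.6 = 1.88. Patent at day 60.

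If the highest pretreatment level was 10, the first two patients show no fall in T-Bil. They fail both items of the primary endpoint (2.8), however those items are combined, yet they are patent.

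**(b) Boundary.** Take 6, 4, 2.5, m, 4, 8, 12.
- m = 1.4: threshold 3.0. Dysfunction.
- m = 1.6: threshold 3.2. Dysfunction.
- m = 1.5: neither rule applies. Patent, although 12/1.5 = 8.

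**(c) Mechanical failure below the threshold.**
- Stent occluded, m = 4.0, T-Bil 7.9 (ratio 1.98, threshold 8.0). Patent.
- Stent occluded, m = 0.8, T-Bil 2.9 (ratio 3.6, threshold 3.0). Patent.

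In both, a CT finding or a re-intervention changes nothing under 2.9, although 2.11 says CT serves "to evaluate the position of the stent, AEs, and stent dysfunction".

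**(d) Time points.** Section 2.9 defines patency to days 30 and 60; section 2.12.2 lists only "and stent patency at 30 days".

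**Size.** With 40 patients in the denominator, each misclassified patient adds 1/40 = 2.5 points. As an illustration, assume a crude result of 38/40 (95% Clopper–Pearson intervals):

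| Reclassified as not patent | Rate | 95% CI |
|---|---|---|
| 0 | 38/40 = 95.0% | 83.1–99.4 |
| 1 | 37/40 = 92.5% | 79.6–98.4 |
| 3 | 35/40 = 87.5% | 73.2–95.8 |
| 5 | 33/40 = 82.5% | 67.2–92.7 |

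**Ceiling for the never-drained group.** Section 2.12.1 assumes 88% clinical success, so (1 − 0.88) × 40 = 4.8 patients without it, and 4.8 × 2.5 = 12 points. This is an upper bound for three reasons:
- Some clinical failures have a draining stent. A fall from 10 to 5.5 leaves 55% of the starting level and, with less than a 50% reduction in duct diameter, is a clinical failure.
- Some have no stent. The Discussion cites 95% technical success for this procedure. If that applied here and the 88% were per enrolled patient (both assumptions), 0.05 × 40 = 2 of the 4.8 would be unstented.
- Some will exceed twice their nadir and be classed correctly.

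**The case against.** **What stands against the point.** Patency is a descriptive secondary endpoint. Failure to drain is already measured by the primary endpoint, and one may prefer patency to mean only loss of function after drainage. If so, the definition must restrict patency to patients who drained; as written, it keeps those who did not and counts them as patent. The gap at 1.5 is a wording slip whose intent is clear, because the rules meet there (2.0 × 1.5 = 3.0), and it matters only if that stent later fails. A fuller protocol or analysis plan may cover day 60, but the article's own list names one of its two time points.

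**Stronger readings that the document does not support.**

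- *Patency is overstated overall, by about 12 points.* Twelve is a ceiling for one group. The rules can also err the other way: a bilirubin rise unrelated to the stent counts as dysfunction, and rule 1 does not say that the value of 3.0 or more must come after the nadir. The net direction is not established.
- *Patients who die are wrongly counted as patent, and a competing-risk estimator would lower the rate.* The article does not say how deaths are handled, which is commonly left to the analysis plan, and a patient who dies may have had a working stent. All patients are followed to death or day 60. Without other dropout there is no censoring, and the cumulative incidence of dysfunction with death as a competing event equals the plain proportion with dysfunction. The estimator would return the same figure.
- *Unstented patients are counted as patent.* Patency runs from stent insertion, so they have no start date. Their place in the denominator is unclear.
- *Migration and occlusion would go unseen.* They are also reported as adverse events, and stent movement is measured on CT at days 1, 14, 30 and 60. The fault is confined to the patency rate.

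**Conclusion.** The point holds for the definition and for the missing time point. Read as written, the dysfunction rules class as patent a stented patient who never drains, any patient with a nadir of exactly 1.5 mg/dL, and an occluded, migrated or re-treated stent whose T-Bil has not crossed the threshold. Sections 2.9 and 2.11 disagree on whether CT can establish dysfunction, and section 2.12.2 omits day 60.

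The size is 2.5 points per misclassified patient, assuming all 40 are in the denominator. For never-drained patients the total cannot exceed about 12 points at the plan's own 88% success, and is probably smaller. The numbers affected by (b) and (c) cannot be derived from the document; (b) should be rare. The primary test does not use this endpoint and is unaffected. The definition should be corrected before patency is analysed.

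**What to change.** 1. In rule 2, change the nadir condition to ≥1.5 mg/dL so that the two rules meet.
2. Add as dysfunction any re-intervention for stent occlusion or migration, and any CT or endoscopic evidence of either. This reconciles 2.9 with the stated purpose of CT in 2.11.
3. Count stented patients in whom drainage was never achieved as not patent, with the criterion for achieved drainage written down. State whether patients without a stent are in the denominator.
4. In 2.12.2, report patency with its Clopper–Pearson interval at both day 30 and day 60.
5. At each time point, report deaths without dysfunction separately, for example by giving the proportion alive and patent beside the crude rate.

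**Cost.** This is wording plus one extra row per time point. Blood tests, CT (days 0, 1, 14, 30 and 60), endoscopy (days 14 and 60), re-intervention and survival are already recorded. The reported patency figure may be somewhat lower. Sample size and the primary analysis do not change.

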### Inclusion criteria

2.4

The following inclusion criteria will be applied.

(1)Age of more than 20 years when providing informed consent.(2)Pathological diagnosis of malignancy.(3)Biliary obstruction due to unresectable malignant tumor.(4)Biliary drainage with ERCP failed, was not possible, or was considered difficult.(5)Serum bilirubin level of higher than 3.0 mg/dL before enrollment.(6)Informed consent document obtained from the patient.

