### Primary endpoint

2.8

The primary endpoint is the clinical success rate, which is defined as follows:

(1)Improvement in the serum total bilirubin (T-Bil) level to below 50% of the highest pretreatment level on at least two of four measuring points including days 3, 7, 14, and 21.(2)A decrease in the T-Bil level after treatment compared with the highest pretreatment T-Bil level, and a decrease in the diameter of the bile duct by 50% or more on day 14 on computed tomography (CT) imaging compared with the largest pretreatment diameter of the bile duct.

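### The stent dysfunction rule in section 2.9(5) cannot detect a return to the pretreatment bilirubin level when the post-treatment low stays at or above half of it, so some initial drainage failures can count as patent

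*Protocol article*

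**What the plan says.** Section 2.9, item (5), of the protocol article defines patency at 30 and 60 days as "the percentage of patients who do not experience stent dysfunction from the date of stent insertion to 30 and 60 days after treatment". Dysfunction has two bilirubin criteria, chosen by how low T-Bil fell after treatment:

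- Low below 1.5 mg/dL: "A T-Bil level of ≥3.0 mg/dL when the lowest T-Bil level measured after treatment is <1.5 mg/dL".
- Low above 1.5 mg/dL: "A T-Bil level more than 2.0 times the lowest level when the lowest T-Bil level measured after treatment is more than 1.5 mg/dL".

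Neither criterion refers to the pretreatment level, to earlier drainage, to imaging or to re-intervention.

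Three other places bear on this:

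- Section 2.4, item (5), sets the entry level: "Serum bilirubin level of higher than 3.0 mg/dL before enrollment".
- Section 2.8 defines clinical success by two items. Item (1) is "Improvement in the serum total bilirubin (T-Bil) level to below 50% of the highest pretreatment level on at least two of four measuring points" (days 3, 7, 14 and 21). Item (2) combines any fall in T-Bil with a reduction of at least half in bile duct diameter on the day 14 CT. The text does not say whether the items are alternatives or are both required.
- Section 2.11 schedules "blood tests on postprocedural days 1, 3, 7, 14, 21, 30, and 60 to evaluate the efficacy of the treatment, AEs, and stent dysfunction" and adds that "CT will be performed postoperatively on days 0, 1, 14, 30, and 60 to evaluate the position of the stent, AEs, and stent dysfunction". It gives no CT criterion for dysfunction.

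Section 2.12.2 reports 30-day patency as a percentage with a 95% Clopper–Pearson interval.

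**The concern.** A rule anchored to the post-treatment low suits a stent that drained well and later failed. It works poorly when the low is itself high, because a high low raises the cut-off. The less bilirubin falls, the further it must climb before the stent is called dysfunctional.

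The denominator is all patients, counted from insertion, and is not limited to those who first drained. A patient whose obstruction was never adequately relieved can therefore be a clinical failure under section 2.8 and a patency success under section 2.9(5). A reader will take the patency rate as a measure of stent function, and the upward bias is largest when initial drainage fails most often.

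**Working it through.** The plan states no patency figure, so there is none to reproduce. The check applies the two criteria as written.

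**Inputs.** P is the highest pretreatment T-Bil, and P > 3.0 mg/dL (section 2.4, reading serum bilirubin there as total bilirubin). L is the lowest post-treatment T-Bil. The criteria are those of section 2.9(5). The target is 40 patients and the expected clinical success is 88% (section 2.12.1).

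**When does a return to P count as dysfunction?**

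1. L < 1.5: the cut-off is 3.0. Since P > 3.0, a return to P is dysfunction.
2. 1.5 < L < P/2: the cut-off is 2L < P. A return to P is dysfunction.
3. L ≥ P/2: since P > 3.0, P/2 > 1.5, so the doubling rule always applies. The cut-off is 2L ≥ P and must be exceeded. A return to P is **not** dysfunction.

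(A low of exactly 1.5 falls under neither criterion. It cannot arise in case 3.)

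**Examples with P = 10 mg/dL**

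| Course after treatment | Cut-off 2L | Scored |
|---|---|---|
| Flat at 10 | 20 | patent |
| Rises from 10 to 19.9 | 20 | patent |
| Rises from 10 to 20.1 | 20 | dysfunction |
| Falls to 7, then 10 on day 30 and 12 on day 60 | 14 | patent |
| Falls to 6, returns to 10 (ratio 1.67) | 12 | patent |
| Falls to 5, returns to 10 (ratio exactly 2.0) | 10 | patent |
| Falls to 4.9, returns to 10 (ratio 2.04) | 9.8 | dysfunction |
| Falls to 2, returns to 10 | 4 | dysfunction |

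The same holds near the entry limit. With P = 3.1 and L = 1.55 the cut-off is 3.1, and a return to 3.1 is patent.

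The switch lies at L = P/2, the same 50% mark that section 2.8 item (1) uses as evidence of drainage. Every patient in case 3 fails item (1).

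**Size.** Expected clinical failures at 88% success: 40 × (1 − 0.88) = 4.8, about 5. If all five are case 3 and all would otherwise be scored patent, the excess is 5/40 = 12.5 percentage points. If none is, the excess is 0.

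Illustration at that ceiling, assuming all 40 are stented and nobody else has dysfunction: as written, 40/40 = 100% (95% Clopper–Pearson interval 91.2 to 100). With the five counted as not patent, 35/40 = 87.5% (73.2 to 95.8).

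**The case against.** The strongest defence is that the protocol separates two questions. Initial drainage is the primary endpoint, and patency then measures loss of function from the best level reached. On that view, clinical failure and no later deterioration can both be true of one patient. The part that stands is that initial failures are not lost to the trial, because section 2.8 captures them. But section 2.9(5) counts all patients from insertion. If patency is meant to describe only those who first drained, the text has to say so.

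Several stronger readings are tempting, and the documents do not support them:

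- *A stent that never drained is always scored patent.* It is scored as dysfunction once T-Bil more than doubles from its low.
- *Failing item (1) of section 2.8 proves drainage failure.* If items (1) and (2) are alternatives, a patient with L ≥ P/2 could still be a clinical success through the CT item. A remedy based on the 50% bilirubin mark alone could then label a primary-endpoint success as a dysfunction from insertion.
- *All clinical failures are misclassified.* A patient below 50% at only one of the four time points can fail item (1), yet has L < P/2, so the existing rule catches a return to P.
- *The rate could be inflated by about 27 points.* That takes the 73% threshold as the true success rate (0.27 × 40 = 10.8 failures) and puts every failure in case 3. The plan expects 88%, so this is not an expected size.

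It may also be said that a stent that does not drain would lead to re-intervention. Re-intervention is reported under item (6) but is not a dysfunction criterion. If another route lowers T-Bil, the rule may never trigger for the first stent.

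**Conclusion.** The point holds in a bounded form. For a patient whose T-Bil never falls below half the pretreatment level, the dysfunction cut-off is at least that full level. A flat course, or a complete relapse to it, is scored patent at days 30 and 60. This is the effect of a rule that is written out, not of detail left to another document, and the scheduled CT does not repair it because no CT criterion enters the definition.

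The amount of bias cannot be known from the documents. At the expected 88% clinical success it lies between 0 and about 12.5 percentage points. The upper end is reached only if every clinical failure stays at or above 50% and would otherwise be scored patent. A reader might infer that the efficacy conclusion is at risk, but it is not. Patency is a descriptive secondary endpoint with no hypothesis test, and neither the primary test against 73% nor the three-patient safety rule uses it.

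**What to change.** Reconcile section 2.9(5) with section 2.8:

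1. State that patients who do not achieve clinical success under the full section 2.8 definition are not counted as patent in the rate over all stented patients. Both items of that definition apply, as the protocol intends them to combine, and not the 50% bilirubin item alone.
2. Report patency separately among patients with clinical success, with the existing dysfunction criteria unchanged.

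The change is one clause and one extra line of results. It uses bilirubin and CT data already scheduled. The cost is a less favourable rate over all stented patients. That rate will also count as not patent a slow responder who first falls below 50% at the day 30 blood test and does not otherwise meet section 2.8. The rate among clinical successes, shown beside it, lets the reader separate initial failure from later loss of function.

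### Re-intervention success is judged against the bilirubin peak before the study procedure, and its drainage-tube condition conflicts with the listed methods

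*Protocol article*

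**What the plan says.** All references are to the protocol article.

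- **Success (2.9, item 6).** Two conditions are joined by an and: a new drain is placed, and there is "improvement in the T-Bil level to below 50% of the highest pretreatment level within 21 days after re-intervention".
- **The same reference in the primary endpoint (2.8).** "Improvement in the serum total bilirubin (T-Bil) level to below 50% of the highest pretreatment level on at least two of four measuring points". Here the reference can only be the peak before the study EUS-HGS.
- **Dysfunction (2.9, item 5).** Either "A T-Bil level of ≥3.0 mg/dL when the lowest T-Bil level measured after treatment is <1.5 mg/dL", or "A T-Bil level more than 2.0 times the lowest level when the lowest T-Bil level measured after treatment is more than 1.5 mg/dL". Both rules start from the nadir after treatment, not from the pretreatment peak.
- **Entry (2.4).** "Serum bilirubin level of higher than 3.0 mg/dL before enrollment", with no upper limit.
- **Methods (2.9, item 6).** The five options include "Treatment from the stent" and "Surgical cholangiojejunostomy".
- **Follow-up (2.11).** Blood tests are set for days 1, 3, 7, 14, 21, 30 and 60 after the procedure. "All patients will be followed until either death or 60 days after the treatment". The article ties no test to the date of a re-intervention.

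**The concern.** A re-intervention success rate should show whether drainage was restored after it had failed. That requires comparing bilirubin after the re-intervention with bilirubin at the time of failure. The stated rule compares it with a value from before the first procedure, which may be several times the level at failure. For some patients the bilirubin condition then asks for no response at all. For others it asks for more than a large and real response can deliver.

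The tube condition raises a second problem. A listed method that places no tube is recorded as a failure however far bilirubin falls. The reported rate would then depend partly on the height of the first peak and on the method used. Few re-interventions are likely among 40 patients, so one or two misclassified cases could change the rate noticeably.

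**Working it through.** The article gives no figure for this endpoint, so there is nothing to reproduce. The check sets the definitions against each other and then against the calendar.

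**1. Can the bilirubin condition already hold at dysfunction?**

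Let B be the peak before the study procedure, N the nadir after it and X the value at which dysfunction is declared, all in mg/dL. The condition is X < B/2.

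- Rule 1 (N < 1.5): dysfunction needs X ≥ 3.0. The overlap is 3.0 ≤ X < B/2, which is non-empty only if B/2 > 3.0, so B > 6.0.
- Rule 2 (N > 1.5): dysfunction needs X > 2.0 × N. The overlap is 2N < X < B/2, which needs N < B/4. With N > 1.5 this again requires B > 6.0.

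The article gives no distribution of B, only that bilirubin exceeds 3.0 at entry. The values of B below are therefore assumptions.

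| B | Limit B/2 | Rule 1: X already below the limit | Rule 2: nadirs for which overlap exists |
|---|---|---|---|
| 6 | 3.0 | none | none |
| 8 | 4.0 | 3.0 to <4.0 | 1.5 to 2.0 |
| 10 | 5.0 | 3.0 to <5.0 | 1.5 to 2.5 |
| 12 | 6.0 | 3.0 to <6.0 | 1.5 to 3.0 |
| 15 | 7.5 | 3.0 to <7.5 | 1.5 to 3.75 |
| 20 | 10.0 | 3.0 to <10.0 | 1.5 to 5.0 |

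(Rule 2 nadir ranges exclude both end points.)

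Examples with B = 12: under rule 1, dysfunction at 3.5 is already below 6.0. Under rule 2, with a nadir of 2.0, dysfunction at 4.1 (> 2.0 × 2.0 = 4.0) is also below 6.0. In both cases bilirubin could even rise further, provided it stays under 6.0, and the condition would still be met.

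**2. Can a real response fail?**

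Take B = 4, so the limit is 2.0. With dysfunction at 10 and a fall to 3 after the re-intervention, the drop is (10 − 3)/10 = 70%. Since 3 is not below 2.0, the patient is a failure.

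**3. The tube condition against the list of methods**

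A surgical anastomosis between bile duct and jejunum is not, read literally, the placing of a drain. Treatment through the existing stent may or may not include one. Where no tube is placed, success is impossible whatever the bilirubin result.

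**4. The 21-day window against the stated schedule**

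For a re-intervention on day d, the scheduled tests that count lie after d and no later than d + 21. The window is complete if d + 21 ≤ 60, so d ≤ 39.

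| Day of re-intervention | Scheduled T-Bil in window | Window complete by day 60? |
|---|---|---|
| 1–20 | at least two | yes |
| 21–29 | day 30 only | yes |
| 30–38 | none | yes |
| 39 | day 60 only | yes |
| 40–59 | day 60 only, 1 to 20 days later | no (window ends on days 61–80) |
| 60 | none | no (window ends on day 81) |

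**The case against.** - **Another reading of the reference.** Inside an item on re-intervention, pretreatment could mean before that re-intervention. If it means the level in the run-up to the re-intervention, steps 1 and 2 fall away. The text does not say this. The same sentence names the re-intervention separately, and section 2.8 uses the phrase for the peak before the study procedure. Nor would a plain maximum over all time before the re-intervention help, because it would still pick up the first peak.
- **The peak before the study procedure is sometimes the right reference.** Re-intervention is not limited to patients who meet the dysfunction rule. Where bilirubin never fell, that peak is a reasonable comparator. This stands, and the fix allows for it.
- **Success before the re-intervention.** A reader might infer that the whole endpoint can be met in advance. It cannot, because the tube must still be placed. Only the bilirubin half can already hold.
- **Treatment through the stent.** A reader might infer that this method can never count. It can if a new tube is placed. Of the listed methods, only the surgical option clearly conflicts on a literal reading.
- **The schedule.** The article is condensed and does not exclude extra tests after a re-intervention. The full protocol may add them. The sentence on follow-up to day 60 gives its purpose as recording survival and concomitant treatment. Early re-interventions are covered in any case. The calendar is therefore only a minor point.
- **Weight.** Section 2.12.2 names no test for this endpoint, and no decision depends on it. This stands and limits the importance of the point.

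**Conclusion.** The definition in section 2.9, item 6, misclassifies some patients if followed as written. With a peak above 6.0 mg/dL before the study procedure, the bilirubin half can already be met when dysfunction is declared, and success reduces to placing a tube. With a low peak, a large fall can count as failure. This rests on reading the reference as section 2.8 uses it. How many patients are affected cannot be derived, since the article gives neither the distribution of peaks nor an expected number of re-interventions.

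The conflict between the tube condition and the surgical option, or treatment through the stent without a tube, holds on either reading of the reference.

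The gap in the schedule (no planned T-Bil in the window for re-interventions on days 30 to 38, and windows passing day 60 from day 40) is secondary and depends on the full protocol adding no tests. It would be wrong to infer that the 21-day window is uncovered in general.

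The primary endpoint, the sample size and the interim safety rule are not touched.

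**What to change.** 1. **Name the reference.** Use the highest T-Bil after the post-treatment nadir and before the re-intervention. If T-Bil never fell after the study procedure, use the highest value before the re-intervention.
2. **Reconcile the tube condition with the list of methods**, so that each listed method can be classified. Which methods belong on the list is a clinical matter and is not judged here.
3. **State how late re-interventions are counted.** Say what happens when no T-Bil falls within 21 days or the window passes day 60, and report the number of incomplete windows. Do not simply exclude patients without a sample. That would remove those who die before one is taken and could inflate the rate. It would also still count days 40 to 59, whose windows are incomplete.

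The cost is a change of wording in section 2.9, item 6. The reported rate may move in either direction: a reference closer to the re-intervention can lower it in patients with a high first peak and raise it in those with a low one, and a reconciled tube condition can raise it.
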